##### Exclusion criteria

Unable to give informed consent.

COLO‐SPEED (group B) aims to establish a C4C database; therefore participation in parallel research studies is encouraged and not an exclusion criterion.

##### Withdrawal criteria

Patients from either group A or group B are withdrawn from the study if they withdraw consent for study participation or withdraw consent to undergo colonoscopy.

### Recruitment process

All eligible and consenting patients are recruited following referral for colonoscopy. COLO‐COHORT commenced just before the COVID‐19 pandemic and, in response to the pandemic, the recruitment process was adapted to minimize the time patients spend in the hospital for research purposes. Patients are contacted via telephone prior to their colonoscopy appointment to assess interest in study participation. If patients are interested in the study, the research team send out a patient information sheet and a FIT (as applicable) and arrange to contact the patient via telephone again at a later date. A pre‐bowel preparation FIT sample is required for the study and therefore those patients who are required to submit a new FIT sample need to be contacted in a timeframe that allows for this. To facilitate the return of FIT samples, patients are provided with a labelled postage paid return envelope. Alternatively, patients can return their FIT to the research team on the day of their colonoscopy.

Patients undergoing a colonoscopy as part of the BCSP are not sent a FIT as this has already been undertaken as part of the screening programme. The same FIT used within the English BCSP (OC Sensor, Mast Diagnostics) is provided to symptomatic patients for uniformity of quantitative FIT results as FIT varies between different manufacturers [32]. Where patients have already undertaken a FIT as part of a symptomatic pathway, the FIT is repeated in this study. The FIT results generated within the study are not directly used to inform patient management through the study; however, local principal investigators are informed of abnormal results and have discretion to act upon these where there is clinical concern.

On the second contact, a member of the research team discusses the study with the patient, answers any questions, assesses eligibility, obtains verbal consent (if the patient is eligible and willing to take part) and gathers other information required for the study.

On the day of the colonoscopy appointment, written informed consent is obtained, anthropometric measurements and blood tests (as applicable per study group) are taken, and patients are recruited into the study.

The adaptations to minimize face‐to‐face contact in response to the COVID‐19 pandemic will be reviewed on an ongoing basis as the pandemic changes and face‐to‐face contact will be reinstated if and where it is considered appropriate.

### Data collection

#### Group A

Six thousand participants in group A (group A1) will submit a pre‐bowel preparation FIT sample. This will be a combination of new FIT collections and samples from patients who have already submitted a FIT sample as part of the BCSP (Figure 1).

**FIGURE 1 codi16160-fig-0001:**
[figure not shown]
Overview of COLO‐COHORT. *10 000 patients in COLO‐SPEED (group B) will be from the north of England and can include patients from group A. **FFQ, food frequency questionnaire [33]. ^§^Patients will be offered the option of limited or more extensive data collection if only in group B.

As approved by the ethics committee, submission of the FIT sample represents initial consent for the study with further information provided in the patient information sheet and full written consent given on the day of colonoscopy. All FIT samples are returned to the northeast BCSP hub at Queen Elizabeth Hospital, Gateshead, for analysis. For patients recruited who are attending colonoscopy because of a positive FIT taken in the BCSP, the quantitative result of that FIT is transferred to the study database.

In addition, a health questionnaire detailing personal characteristics (level of education, employment status), lifestyle behaviour (smoking status and alcohol intake history), medical and medication history, and family history of CRC is completed, as well as a validated physical activity questionnaire and validated food frequency questionnaire for those undergoing microbiome analysis [33, 34]. In the light of the COVID‐19 pandemic, questionnaires may be completed remotely from the endoscopy unit. Postage paid envelopes are provided by the research team to facilitate the return of completed questionnaires.

At the colonoscopy appointment, height, weight and waist circumference are measured. In addition, blood samples for full blood count, liver function tests, aspartate aminotransferase, C‐reactive protein, lipid profile, fasting glucose, HbA1c, and whole blood for DNA extraction are taken, via a cannula inserted as part of standard care for colonoscopy. Where sampling is not possible from a cannula, a separate venepuncture is undertaken. These tests are not repeated if results from within the last 8 weeks are available. All blood tests other than the blood sample for DNA extraction are labelled and processed in line with local Trust policy in local laboratories. The sample for DNA is pseudonymized using a unique study ID and transferred to the Central Biobank Facility at Newcastle University. Samples are stored at −80°C until thawed in preparation for DNA extraction; following extraction genomic DNA is stored at −80°C.

Patients' colonoscopy findings are recorded along with histopathology results from any lesion removed or sampled. Diagnosis of neoplasia is based upon histological findings.

A further 4000 patients will be recruited into group A (group A2). Although the dataset recorded is similar to group A1, patients are not required to collect stool for the FIT nor have blood samples taken. This allows patients who are unable or unwilling to provide biosamples to participate in this part of the study. These patients will provide the research team with a significant amount of useful data to enhance or potentially validate data from the A1 group. Any recent blood tests of interest in the past 8 weeks prior to their colonoscopy (as a minimum, full blood count and liver function tests) as well as FIT results if done as part of routine care are recorded.

All patients from group A are asked if they also consent to the following:
long‐term follow‐up for future outcome related to colorectal polyps or CRC through linkage to routine national databases such as National Cancer Registration Database, Hospital Episode Statistics data, Office for National Statistics mortality data, National Endoscopy Database and the COloRECTal cancer data Repository (CORECT‐R) [35];access to previous endoscopy results, histological samples from colonoscopy or other relevant laboratory results;use of anonymized information or samples collected from this study in future studies;consent for future contact for collection of additional information related to this study.

Patients may opt into or out of each of these.

### Microbiome

Stool microbiome analysis is performed using the stool sample submitted for the FIT. The rationale for this is based upon our pilot work that demonstrated excellent agreement with fresh stool analysis and the stability of microbiome diversity and taxonomic profiles when using the FIT test kit (OC Sensor, Mast Diagnostics) for microbiome analysis [36].

Microbiome analysis is performed on all new FIT collections and (subject to patient consent) on positive BCSP FIT samples that were analysed by the northeast BCSP hub. Patients undergoing microbiome testing are asked to complete the EPIC food frequency questionnaire for dietary information [33].

Once the FIT is performed, the pseudonymized samples (labelled with unique study ID) are transferred to the Central Biobank Facility at Newcastle University. Samples are frozen (at −80°C) on arrival at the Biobank Facility; batched samples are then thawed and isolation of faecal DNA is performed using the DNeasy PowerLyzer PowerSoil Kit (QIAGEN). The QIAcube HT provides automation for this process and facilitates the extraction of faecal DNA in a timely manner. Microbiome analysis will then be performed at the University of Leeds and Newcastle University.

Stool microbiome analysis is a rapidly evolving field [21, 22]. In the first instance, we propose to measure microbiome diversity and individual pathobionts by 16S rRNA sequencing but will remain flexible with our approach to, for example, shotgun metagenomic sequencing based on subsequent developments in the field, DNA yields from FIT stool extractions and our funding envelope [36, 37] (Table 1).

**TABLE 1 codi16160-tbl-0001:** Summary of data collection for group A

Questionnaire	Measurement	Sampling	Colonoscopy
Health questionnaire Physical activity questionnaire FFQ^a^	Height Weight Waist circumference	Stool for FIT^b^ Blood tests	Colonoscopy report Histology report

Abbreviations: FFQ, food frequency questionnaire; FIT, faecal immunochemical test.

^a^
Patients undergoing microbiome analysis only.

^b^
Non Bowel Cancer Screening Programme patients.

#### Group B (C4C; COLO‐SPEED)

Patients from group A can also be recruited into group B.

Patients are recruited to COLO‐SPEED from northeastern recruitment sites, with the longer‐term vision of expanding to other sites nationally, subject to securing funding.

All patients consenting to group B consent to being contacted about future research involvement opportunities, including relevant research studies, patient and public involvement (PPI) opportunities and public engagement activities. They will be sent a link to register online for the COLO‐SPEED Research Network (CSRN).

In addition to consent for future contact, patients are asked if they wish to consent to the following:
long‐term follow‐up for future outcome related to colorectal polyps or CRC through linkage to routine national databases such as the National Cancer Registration Database, Hospital Episode Statistics data, Office for National Statistics mortality data, National Endoscopy Database and the CORECT‐R [35];access to previously collected endoscopy results, histological samples from colonoscopy or other relevant laboratory results;use of anonymized information or samples collected from this study in future studies;consent for future contact for collection of additional information related to this study.

Group B patients are offered the choice of limited data collection or more extensive data collection. Limited data collection includes their age, sex, ethnicity, family history, height and weight measurements, indication for colonoscopy, and colonoscopy and histology results (where applicable). More extensive collection comprises, in addition to the elements of the limited collection, the health questionnaire and the recording of recent blood results (within the past 8 weeks) and/or FIT results if available.

No new samples (blood or stool) are taken from COLO‐SPEED (group B) patients unless they are also part of group A.

### Nested studies

COLO‐COHORT will recruit a large population, and appropriate nested studies, for example collecting data on patient experience of colonoscopy or impact of COVID‐19 on colonoscopy uptake and experience, may be incorporated into the study (subject to additional ethical approval where required).

### Adverse events

This is an observational study and therefore no adverse events resulting from participation are anticipated. Any adverse events related to colonoscopy will be managed and recorded in line with standard care.

### Assessment and follow‐up

No additional study visits are required as part of the study. However, patients may receive a maximum of two reminders at monthly intervals to complete the patient questionnaires (outlined above), if required.

Patients who consent to long‐term follow‐up may have their endoscopy records and medical records interrogated for outcomes related to colorectal neoplasia as described above.

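### Questionnaire predictors have no cut-off relative to colonoscopy, so some can be reported after the patient knows the result

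*Protocol article*

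**What the plan says.** *Recruitment process* places written consent and enrolment on the day of the procedure: "On the day of the colonoscopy appointment, written informed consent is obtained", and later in the same sentence "blood tests (as applicable per study group) are taken, and patients are recruited into the study". Before that there are two telephone contacts. At the second, a team member "gathers other information required for the study", but the questionnaires are not named there.

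*Data collection, Group A* describes a health questionnaire covering education, employment and "lifestyle behaviour (smoking status and alcohol intake history), medical and medication history, and family history of CRC is completed". It adds a physical activity questionnaire and, for microbiome patients only, a food frequency questionnaire. Because of the pandemic, "questionnaires may be completed remotely from the endoscopy unit". The return route is by post: "Postage paid envelopes are provided by the research team to facilitate the return of completed questionnaires".

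*Assessment and follow-up* opens with "No additional study visits are required as part of the study" and then gives the exception: "patients may receive a maximum of two reminders at monthly intervals to complete the patient questionnaires", if required.

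*Statistical analysis and sample size* defines the primary outcome as advanced adenoma or CRC at the recruitment colonoscopy. It enters patient characteristics and lifestyle as candidate predictors in the logistic model. Dietary data appear separately, combined with the microbiome to compare groups defined by colonoscopy result.

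**The concern.** The model is meant to decide who should have a colonoscopy, so its predictors should be those available before the procedure. An answer given afterwards may differ for two reasons. A patient told of a cancer or advanced adenoma may search memory harder, or ask relatives, about family history. Smoking, alcohol, medication, activity or employment may also really have changed since the diagnosis. Either effect ties the predictor to the outcome in a way that would not exist when the model is used. The direction is not fixed: fuller recall inflates an association, whereas a smoker who stops after diagnosis and reports the new status weakens one.

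The planned internal validation would not show this. Bootstrap samples are drawn from the same data. Leaving out one site at a time does not isolate the effect, because the reminder rule applies across the study. Optimism-corrected performance could look sound while some coefficients fail to carry over to pre-colonoscopy use.

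**Working it through.** **Timing, from the text.**

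1. Outcome: neoplasia at the recruitment colonoscopy (*Statistical analysis and sample size*).
2. Enrolment: the same day (*Recruitment process*).
3. Questionnaires: may be completed remotely and returned by post (*Data collection, Group A*).
4. Reminders: up to two, a month apart, described under follow-up (*Assessment and follow-up*). If the first goes out a month after issue, the second falls about two months after issue. Unless issue precedes colonoscopy by at least that long, a reminder falls after the procedure.
5. Timing rules for other predictors: FIT must precede bowel preparation, and blood results are accepted from the previous 8 weeks. The only stated timing rule for questionnaires extends their collection.

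Followed as written, the plan admits some predictors reported after the result.

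**Possible size.** The article gives no figure to reproduce, and it states neither the share of late questionnaires nor any reporting error. All inputs below are assumptions.

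- True odds ratio 1.0 for a yes/no item such as family history; true prevalence q = 0.15.
- s0 = probability that a true positive is reported by non-cases, and by cases answering before the result; s1 = the same for cases answering after it.
- L = share of cases answering late, 0.20 or 0.40.
- Late non-cases report as they would have before; there are no false positives.

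Apparent OR = odds(q × [(1 − L) × s0 + L × s1]) / odds(q × s0), where odds(p) = p/(1 − p).

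With s0 = 0.75 and s1 = 0.95, the reference is 0.15 × 0.75 = 0.1125, odds 0.1268.
- L = 0.20: 0.15 × 0.79 = 0.1185, odds 0.1344, OR 1.06.
- L = 0.40: 0.15 × 0.83 = 0.1245, odds 0.1422, OR 1.12.
- Late responders alone (L = 1): 0.15 × 0.95 = 0.1425, odds 0.1662, OR 1.31.

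With s0 = 0.80 and s1 = 0.90, the reference is 0.15 × 0.80 = 0.1200, odds 0.1364.
- L = 0.20: 0.15 × 0.82 = 0.1230, odds 0.1403, OR 1.03.
- L = 0.40: 0.15 × 0.84 = 0.1260, odds 0.1442, OR 1.06.
- Late responders alone: 0.15 × 0.90 = 0.1350, odds 0.1561, OR 1.14.

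The overall range is 1.03 to 1.12.

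A wider grid (q 0.15 to 0.30, L 0.10 to 0.50, s0 = 0.70, s1 = 0.80 or 0.90) runs from 1.02 to 1.19. The low end is odds(0.1065)/odds(0.1050) = 1.016; the high end is odds(0.24)/odds(0.21) = 1.188.

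**The case against.** The article does not say when the reminder clock starts. Two calls precede colonoscopy, the second collects study information, and remote completion was introduced to shorten time in hospital, which fits completion at home beforehand. Reminders are sent only if required, and two is the maximum. This stands: the text shows that late completion is permitted, not that it is usual. A reader might infer that questionnaires are routinely completed one to two months after the result, and the documents do not support that.

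The article is condensed and promises a full statistical analysis plan, where handling of late forms could properly sit. That is fair for the analysis rule. It does not remove the collection rule, which the article does state and leaves open-ended. If completion dates are not captured during recruitment, a later plan cannot separate early from late answers; the article does not say whether they are captured.

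The illustration rests on invented inputs. It gives every late case the full rise in reporting, including patients with an advanced adenoma, and gives late non-cases none. Family history is already the referral reason for some patients, and several items are histories that a diagnosis does not change. These points stand, so the figures only indicate scale.

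Two further inferences are tempting. One sets the illustration beside the odds ratio of 1.13 that the article calls detectable. That benchmark does not hold: the article's own formula with SE = 0.125 gives V = 0.125² × 6000 = 93.75, β = √(8 × 93.75/6000) = 0.354 and an odds ratio of 1.42. The other treats diet as a predictor in the main model. The article names it only in the microbiome comparison and collects it only from microbiome patients.

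**Conclusion.** The concern holds in a limited form. Enrolment on colonoscopy day, postal return and monthly reminders with no cut-off together allow some self-reported predictors to be recorded after the outcome is known to the patient. The same applies to diet in the microbiome comparison, where the groups are themselves defined by the colonoscopy result. That is a weakness for a model intended for use before the procedure, and the planned bootstrapping and cross-validation would not detect it.

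How often it happens and how much bias follows cannot be known from the article. An overall odds ratio of 1.03 to 1.12 for a null predictor depends on the assumed prevalence, late share and reporting sensitivities, and the true effect may be smaller. The conclusion also relies on reading the reminders, placed under follow-up, as able to fall after colonoscopy. The point merits a change because the remedy is cheap and depends on data captured during recruitment.

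**What to change.** 1. Issue the questionnaires at the pre-colonoscopy contacts and, where the waiting time allows, send reminders before the procedure. Tie this to the contacts rather than to the FIT mailing, because screening-programme patients are not sent a FIT and group A2 patients are not required to provide stool.
2. Record the completion date of each questionnaire, if this is not already done.
3. Pre-specify a sensitivity analysis that refits the risk model using only questionnaires completed on or before colonoscopy day, and report any change in coefficients, discrimination and calibration. Repeat the diet–microbiome comparison under the same restriction.

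Excluding late questionnaires from the primary model is not required. It would drop patients according to response behaviour, which may itself relate to lifestyle and outcome.

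The cost is one date field, a small change in mailing order, a few lines in the statistical analysis plan, and lower precision in the restricted analysis. For patients already recruited, the restriction can be applied only where a completion or receipt date exists.

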### Statistical analysis and sample size

Data from patients recruited to group A will be used to develop the risk prediction model. Primary analysis will be based on the outcome of the presence of colorectal neoplasia at the recruitment colonoscopy. This will be defined as the presence of advanced adenoma (AA)/CRC. AA will be defined as an adenoma of at least 10 mm in size or containing high‐grade dysplasia [38]. Secondary analyses will focus on other relevant outcomes, including CRC (only), AA (only), any adenoma, any polyp, serrated polyps, numbers of adenomas and number of polyps. The TRIPOD statement will be followed for reporting of the risk prediction model [39].

Initially we will develop models separately for BCSP and other (mainly symptomatic) subjects; further analysis will explore whether an overall model can be created. Firstly (in the non‐BCSP subjects), sensitivity, specificity, positive predictive value and negative predictive value of FIT alone for the detection of the presence of AA/CRC will be assessed. Different FIT cut‐offs will be explored. Subsequently, the relationship between patient characteristics and lifestyle, phenotypic information, FIT results, blood markers and presence of AA/CRC will be investigated using logistic regression. Backwards elimination of candidate predictors will be used to identify variables which best predict neoplasia [40]. Receiver operating curve plots, area under the curve analyses of sensitivity and specificity, and Harrell's C‐index will be used to characterize the discriminative ability of the models [41, 42]. Calibration will be assessed using Hosmer and Lemeshow tests, the percentage of people reclassified by different models and the net reclassification index [43]. Internal validation will be undertaken using bootstrapping to quantify the model's potential for overfitting and optimism in estimated model performance [40]. Cross‐validation approaches will also be applied, systematically excluding groups of subjects (e.g., by site) in turn [44]. In addition, multinomial, or ordinal, logistic regression will be used to investigate predictors of the secondary outcomes. Multiple adenomas may occur in an individual. It is anticipated that the presence of multiple adenomas will be zero‐inflated, with some patients having zero and others many. The extent to which zero‐inflated models (e.g., allowing for aggregation) improve the prediction of the presence of adenomas will be assessed.

The microbiome data will be subjected to canonical correspondence analysis to identify (i) major trends in variation across the patient cohort and (ii) putative drivers of the variation in each patient subgroup (defined on the basis of colonoscopy result: CRC, advanced adenomas, non‐advanced adenomas, sessile serrated polyps and clear colon). Canonical correspondence analysis seeks to explain the pattern of variation in complex (multivariate) datasets using covariates hypothesized to be of significance in causing variation. We hypothesize that there will be differences in microbiome composition that will be dependent on the adenoma/disease status of patients and that these may act as markers for disease. We will use similar approaches to determine whether dietary data, when combined with the microbiome, reveal further differences between groups. Correspondence analysis will be used to provide summaries of the variation microbiome to allow for investigation of the contribution of microbiota profile to the risk prediction models.

The study is exploratory in nature—particularly in relation to whether microbiome data make an important contribution to risk prediction models. Therefore the sample size calculation must be governed by principles of adequate population size.

The sample size of patients providing biosamples (6000) is based on the power calculation by Peduzzi et al. [45]: sample size *N* = 10(*k*/*p*), where *k* is the number of covariates to be investigated in the model and *p* is the smallest of the proportions of positive or negative cases.

Using Demidenko's method, the sample size needed for logistic regression with 80% power and 5% level of significance is *N* = 8*V*/*β*2, where *β* is the natural log of the odds ratio and *V* is logistic model variance due to covariates [46]. This formula can be rearranged to determine the minimum odds ratio that can be detected at a sample size of 6000 with sufficient power. Assuming a moderate standard error in the regression (SE = 0.125) and calculating *V* from the standard error (*V* = (SE√*N*)2) the study will have sufficient statistical power to detect an effect with a small effect size with an odds ratio of 1.13.

Group B sample size is based upon generating a significant but manageable C4C population.

A full statistical analysis plan will be developed prior to data analysis.

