## Abstract

**Aim:**

The COLO‐COHORT study aims to produce a multi‐factorial risk prediction model for colorectal neoplasia that can be used to target colonoscopy to those at greatest risk of colorectal neoplasia, ensuring that people are not investigated unnecessarily and maximizing the use of limited endoscopy resources. The study will also explore the link between neoplasia and the human gut microbiome. Additionally, the study aims to generate a cohort of colonoscopy patients who are ‘research ready’ through the development of a consent‐for‐contact (C4C) platform, to facilitate a range of colorectal cancer prevention studies to be conducted at scale and speed.

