## DISCUSSION

Development of risk adapted triage for colonoscopy has been identified as a research priority [49]. COLO‐COHORT will produce a multi‐factorial risk prediction model for colorectal neoplasia based upon a large cohort of patients attending for colonoscopy at sites with diverse catchment populations. Following external validation, this model can then be used to inform more intelligent colonoscopy, directing limited endoscopy resources to those individuals at highest risk and additionally avoiding unnecessary investigations for those at low risk. It is acknowledged that several recent studies have demonstrated the value of the FIT in CRC risk prediction, but this study goes significantly further by looking more widely at neoplasia and considering factors not included in many of the previous FIT studies, notably the microbiome. As risk models are developed, they have potential to be applied to other datasets for validation.

The study will provide large‐scale gut microbiota analysis in both symptomatic and screening patients aiding the understanding of the role of the gut microbiome and its association with colorectal neoplasia. The study will adopt the large‐scale use of FIT samples for microbiome analysis. The FIT is used widely, within the national BCSP and with increasing use in the symptomatic setting. The wide availability of these samples has cost saving implications for the study (and for future application of the approach) and increased convenience for patients, with only one sample required [36].

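### The only measures named for comparing models are the percentage reclassified and the net reclassification index, which are listed as calibration and can favour the worse triage tool

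*Protocol article*

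**What the plan says.** The Abstract gives the purpose as targeting colonoscopy, "ensuring that people are not investigated unnecessarily and maximizing the use of limited endoscopy resources". The Discussion foresees use of the model, once externally validated, for "directing limited endoscopy resources to those individuals at highest risk and additionally avoiding unnecessary investigations for those at low risk". That is a triage tool.

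The section on statistical analysis and sample size then assigns performance measures.

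- **FIT alone, non-BCSP patients:** "sensitivity, specificity, positive predictive value and negative predictive value of FIT alone for the detection of the presence of AA/CRC will be assessed". It adds: "Different FIT cut‐offs will be explored".
- **Discrimination of the models:** "Receiver operating curve plots, area under the curve analyses of sensitivity and specificity", together with Harrell's C-index.
- **Calibration and comparison of the models:** "Calibration will be assessed using Hosmer and Lemeshow tests, the percentage of people reclassified by different models and the net reclassification index".
- **Internal validation:** "Internal validation will be undertaken using bootstrapping to quantify the model's potential for overfitting and optimism in estimated model performance", plus cross-validation, for example by site.

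The section does not say which models the reclassification measures would compare, or with which risk categories.

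**The concern.** Two things in the stated method fit the purpose poorly.

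First, the percentage reclassified and the net reclassification index are presented as ways to assess calibration. Calibration is agreement between predicted and observed risk, and of the three measures listed only the Hosmer-Lemeshow test addresses it. The percentage reclassified counts people who change risk category, whether or not the move was right. The index summarises the direction of those moves in people with and without the outcome.

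Second, these two are the only measures named for setting one model against another. In its usual two-category, summed form the index gives a point of sensitivity and a point of specificity equal weight, whatever the prevalence and whatever a missed lesion is worth relative to an unnecessary colonoscopy. A tool that spares low-risk people colonoscopy works at risk thresholds below prevalence. There a lost point of sensitivity costs more than a gained point of specificity returns. The index could therefore support a claim that the model improves on FIT when, at the thresholds that matter, the model does the triage job less well.

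**Working it through.** The documents give no figure to reproduce here: no prevalence of advanced adenoma or cancer (AA/CRC), no risk threshold and no expected accuracy. The inputs below are assumptions for illustration, and none is a proposed threshold.

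**Formulas.** Let p be prevalence, t the risk threshold, and dSens and dSpec the model's sensitivity and specificity minus those of FIT.

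- Two-category index = dSens + dSpec. A simulation of 200,000 patients confirmed that its two components equal the changes in sensitivity (+0.0895 both ways) and in specificity (+0.0099 both ways).
- Change in net benefit = p × dSens + (1 − p) × [t/(1 − t)] × dSpec.
- At t = p the second formula becomes p × (dSens + dSpec), so the two measures are proportional there. Below p, the index gives specificity too much weight relative to net benefit.

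**Illustration.** Assume p = 0.10, dSens = −0.05, dSpec = +0.08.

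- Index: −0.05 + 0.08 = +0.03, so the model looks better.
- Per 1000 patients: 100 × 0.05 = 5 more AA/CRC missed, and 900 × 0.08 = 72 fewer unnecessary colonoscopies (total referrals fall by 77). That is 72/5 = 14.4 unnecessary colonoscopies avoided per extra lesion missed.
- Net benefit at t = 0.03: −0.0050 + 0.90 × (0.03/0.97) × 0.08 = −0.0050 + 0.0022 = −0.0028, or −2.8 per 1000. A 3% threshold implies an exchange rate of 0.97/0.03 = about 32 to one, which 14.4 does not reach.
- Net benefit at t = 0.10: −0.0050 + 0.90 × (0.10/0.90) × 0.08 = +0.0030, or +3.0 per 1000.
- Break-even: t/(1 − t) = 0.005/0.072 = 0.069, so t is about 6.5%. Above that the two measures agree in sign.

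**Range over prevalence**, same dSens and dSpec. The index is +0.03 throughout. Break-even odds are (0.05/0.08) × p/(1 − p).

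| Assumed prevalence | Change in net benefit at t = 3%, per 1000 | Break-even t |
|---|---|---|
| 5% | −2.5 + 2.35 = −0.1 | 3.2% |
| 10% | −5.0 + 2.2 = −2.8 | 6.5% |
| 20% | −10.0 + 2.0 = −8.0 | 13.5% |

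**Does the AUC settle it instead?** Not on its own. Under a binormal ROC curve with AUC 0.80, sensitivity at 90% specificity is 58%, 46% or 34% for slope 0.6, 1.0 or 1.5.

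**Why matched referral rates help.** If FIT and the model send the same number to colonoscopy, then p × dSens = (1 − p) × dSpec. The two changes then share a sign, and the index and net benefit cannot point in opposite directions.

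**Why misses should be split.** If cancers were 25% of AA/CRC cases (assumed), a composite sensitivity of 90% would be compatible with a cancer sensitivity as low as (0.90 − 0.75)/0.25 = 60% or as high as 100%. These are bounds, not an expected result.

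**The case against.** The strongest reply is that the article condenses a longer plan and promises a full SAP. A risk threshold, predictive values for the model and a table per 1000 patients are ordinary SAP content. That stands: their absence from the article is no fault by itself.

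A reader might also infer that the models are scored only on AUC and reclassification. They are not: ROC plots, the C-index, Hosmer-Lemeshow tests, bootstrapping and cross-validation are all planned.

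A reader might go further and infer that the study cannot say how many colonoscopies the model spares or how many lesions it misses. The documents do not support that either. Group A patients all attend colonoscopy, and findings and histology are recorded. A ROC plot shows sensitivity and specificity at every cut-off, and the cohort supplies its own prevalence. CRC only and AA only are named secondary outcomes, so misses could be split by type.

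Nor does the article state that its question is whether the model beats FIT. The first objective is to develop a risk model, and FIT is one of its inputs.

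Finally, the index is not declared decisive, its categories are not fixed, and its two components reported separately would give the changes in sensitivity and specificity. This is fair, and it limits the point to the summed index used as the basis for a claim. It does not remove the point: the section does choose reclassification as its named between-model measure and does call it calibration. A SAP that follows the text would carry both over.

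**Conclusion.** The point holds as a weakness in a stated method. Reclassification is wrongly placed under calibration; that needs no assumptions. As a comparison measure, the summed index suits a triage tool poorly, because below prevalence it can reward a model with lower net benefit.

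The size shown, an index of +0.03 against −2.8 per 1000 at a 3% threshold, rests on an assumed 10% prevalence, assumed accuracy changes and a two-category index. The conflict disappears above a threshold of about 6.5% on those inputs. It arises only when a model gives up sensitivity for specificity; the two measures can agree in sign away from t = p. The illustration shows that a misleading result is possible, not that it is likely. The matter is worth settling before analysis but does not threaten the study's data.

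**What to change.** In the section on statistical analysis and sample size, and in the SAP that follows it:

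1. Stop listing the percentage reclassified and the net reclassification index as calibration measures.
2. Base any claim that the model adds to FIT on optimism-corrected net benefit (a decision curve) over a threshold range that the sponsor sets before the analysis.
3. Report sensitivity, specificity, PPV and NPV for the model and for FIT alone at matched referral rates: for each FIT cut-off, use the model threshold that sends the same number to colonoscopy. Correct the model's figures for optimism with the bootstrap already planned.
4. Make this comparison in the same non-BCSP patients with a FIT result. Many BCSP patients enter because of a positive FIT, and group A2 patients have a result only if one was done in routine care.
5. Split missed lesions into CRC and AA.

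The cost is a little more analysis on data already to be collected, with no new patients or procedures. The downside is that an apparent gain on AUC or reclassification may shrink.
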